### 2.11 Statistical analysis

To ensure that the baseline characteristics of participants in the SHG treatment and control groups are the same, a propensity score approach will be used. Variables involving factors such as age, gender, smoking and drinking history, and body mass index will be included in a logistic regression model to calculate a propensity score for each participant. Participants using SHG will be matched to control participants based on propensity scores, using greedy matching with a standard caliper width of 0.2 and without case replacement. The two groups’ baseline characteristics will be summarized by descriptive statistics. Baseline demographic variables will be presented as means, medians, or percentages, and using Chi-square test, independent t-test, or Mann-Whitney U test, as appropriate.

The quantitative data will be processed and analyzed by an independent statistician using PASW 18.0 (IBM SPSS Inc., Armonk, New York, United States). We will conduct preliminary analysis on the full analysis population following the Intention-to-Treat (ITT) principle. The full analysis population included all randomized participants who received at least one dose of study drug, but excluded patients who were erroneously included or did not receive any assigned treatment or follow-up. The per-protocol set is a subset of the full analysis set and includes patients who completed the predetermined minimum exposure to trial drug and completed follow-up. Safety analysis will be performed on the randomized participants who received at least one dose of SHG or placebo and were evaluated for safety. Changes from baseline to post-treatment in ISI, PSQI, FSS, PHQ-9 and GAD-7 will be analyzed. The results of the two groups will be analyzed using analysis of covariance with associated 95% confidence intervals. The Bonferroni correction method is used for multiple comparisons. For example, if ISI compares three times, the significant level after correction is 0.05/3 = 0.0167. Only when the P value is less than 0.0167, we think that the difference between the group is statistically significant.

An ITT analysis will be conducted utilizing the imputation method to address missing data. It is anticipated that the proportion of missing data points will be less than 20%. The linear trend at point method will be employed to substitute missing values. In this approach, the existing data series will be regressed against an index variable that is scaled from 1 to n, allowing for the replacement of missing values with their corresponding predicted values. In instances where predicted values cannot be determined, the last observation carried forward (LOCF) method will be implemented. Additionally, a sensitivity analysis will be performed without imputation to evaluate the robustness of the findings.

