### 2.2 Trial design

This is a single-center, randomized, double-blind, parallel group, placebo-controlled clinical trial. The trial will be conducted in the Guangdong Provincial Hospital of TCM. A total of 160 eligible participants will be randomized into the experimental group (SHG) or the control group (placebo) with a 1: 1 ratio. The duration of the intervention is 4 weeks and the total observation follow-up period will be 8 weeks. Study visits will take place at baseline and at 2, 4, 6, 8 weeks. Each patient will be asked to visit within 3 days of the given time point. All participants will be required to sign the written informed consent (Supplementary Material 6, 7) before randomization. This protocol was compiled in line with the Standard Protocol Items: Recommendations for Interventional Trials (SPIRIT) Guidelines (Supplementary Material 8; Chan et al., 2013). The flowchart of this trial is presented in Figure 1. The schedule of enrollment, interventions, and assessments is as shown in Table 2.

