### 2.5 Randomization and allocation

The random sequence will be generated by the central randomization system from Guangdong Provincial Hospital of Chinese Medicine. Participants will be randomly allocated into either the treatment or placebo group, at a ratio of 1:1. Patients in the treatment group (n = 80) will receive the treatment of SHG, while patients in the placebo group (n = 80) will receive placebo granules, that are identical in appearance to the SHG. Stratified by the central stratification method, we will use SAS 9.2 statistical software to generate random numbers and the random assignment results. The investigators will obtain the randomized number and drug number by a sequential number in the central randomization system. All center numbers, sequence numbers, randomization numbers, and drug numbers will be managed by the statistical unit.

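### Section 2.11 prescribes propensity-score matching in a trial already randomised 1:1, contradicts its own ITT full analysis population, and does not say which set is primary

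*Protocol article*

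**What the plan says.** Section 2.2 of the protocol article sets the design: "A total of 160 eligible participants will be randomized into the experimental group (SHG) or the control group (placebo) with a 1: 1 ratio". Section 2.5 repeats it: "Participants will be randomly allocated into either the treatment or placebo group, at a ratio of 1:1", with 80 patients per arm.

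Section 2.11 opens with a different device. So that baseline characteristics "in the SHG treatment and control groups are the same, a propensity score approach will be used". The score comes from a model in which "age, gender, smoking and drinking history, and body mass index will be included in a logistic regression model to calculate a propensity score"; these variables are introduced as examples, not as a closed list. The rule follows: "Participants using SHG will be matched to control participants based on propensity scores, using greedy matching with a standard caliper width of 0.2", without replacement. Neither the scale of the caliper nor the matching order is given.

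The next paragraph of 2.11 places the analysis on the "full analysis population following the Intention-to-Treat (ITT) principle". That population is all randomised patients with at least one dose, less those wrongly included or without any treatment or follow-up. The arms are compared by analysis of covariance with 95% confidence intervals.

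Section 2.10 asks for 128 patients and raises this to 160 for a 20% loss to follow-up.

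**The concern.** Matching on a propensity score is a device for non-randomised comparisons, where treatment choice depends on patient characteristics. Here allocation is random at 1:1, so the true propensity is 0.5 for everyone. A fitted score describes only chance imbalance, and the planned ANCOVA can adjust for that while keeping every patient.

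Matching without replacement inside a caliper leaves out each patient who has no near partner. Who is left out depends on the fitted score, the caliper scale and the matching order. A set formed in this way is not the full analysis population defined a paragraph later, and the plan does not say which of the two carries the primary result.

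At stake are whether the primary comparison is the randomised one, how many patients it contains, and whether that choice could still be made after the data are seen.

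**Working it through.** **1. The passages side by side.** The matching is stated without condition and is not labelled secondary, exploratory or a sensitivity analysis. The full analysis population is also stated without reference to matching, and lack of a partner is not a listed exclusion. If any patient is unmatched, the two sets differ. The sentence that invokes ITT calls that analysis preliminary, so it does not settle which set is primary.

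**2. The plan's own figure.** 128 / (1 − 0.20) = 160, as stated. The allowance is used up by loss to follow-up, and nothing is left for unmatched patients.

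The 128 itself cannot be derived uniquely from an effect size of 24.3%, because no SD or placebo value is given. It does agree with a standardised difference d = 0.5 at 80% power and one-sided 0.025 (equivalently two-sided 0.05): the t-test needs 64 per arm, 128 in total. I therefore take d = 0.5 as an **assumption**.

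**3. How many pairs survive.** I simulated 1,500 randomised trials per setting. Each had five baseline covariates unrelated to allocation, a logistic score, and greedy pair matching without replacement in random order. Assumed covariates: age SD 12, BMI SD 3, binary rates 20-35%. Because the caliper scale is not stated, three readings are shown. Brackets give 5th-95th percentiles where available.

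| Reading of the 0.2 caliper | Mean pairs from 80 v 80 | Mean pairs from 64 v 64 |
|---|---|---|
| 0.2 SD of the logit | 64 (58-70) | 49-50 (44-54) |
| 0.2 on the logit | 69 | 54 |
| 0.2 on the probability | 77 (71-80) | 61 (54-64) |

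Smallest share dropped: (80 − 77)/80 = 4%. Largest: (64 − 50)/64 = 22%. At 0.2 SD of the logit every simulated trial lost at least one pair. On the probability scale 73-78% of trials did.

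**4. Power if the matched set were primary.** Two-sample t-test, two-sided 0.05, 2n − 2 degrees of freedom, noncentrality d × √(n/2). For n = 64 this is 0.5 × √32 = 2.83; for n = 50 it is 0.5 × √25 = 2.50.

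With the full 20% dropout:
- 64 per arm, no matching: 80%
- 61 pairs: 78%
- 54 pairs: 73%
- 49-50 pairs: 69-70%

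Matching at baseline and then losing 20% gives much the same at the strict caliper: 64 × 0.80 = 51 pairs, power 71%.

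With no dropout:
- 80 per arm, no matching: 88%
- 77 pairs: 87%
- 69 pairs: 83%
- 64 pairs: 80%

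**The case against.** The strongest defence is that 2.11 never says the ANCOVA is run on matched pairs. The matching stands in the paragraph on baseline comparability, while the ANCOVA comes in the next paragraph, with the full analysis population. The passage on missing data again promises an ITT analysis. On that reading the randomised comparison survives. This stands as a limit: a reader might infer that patients are certain to be discarded and the ITT result lost, and the text does not establish that. It does establish two instructions that are not reconciled.

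Three other stronger readings also fail:

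- **Baseline ISI is excluded from the score.** It is not named, but the list is open, so exclusion is not shown.
- **Power falls from 80% to 53%.** That compares 64 per arm at 0.05 with 50 per arm at the Bonferroni level of 0.0167, which 2.11 gives only as an example. At 0.0167, 64 per arm without matching already gives 66%. Matching accounts for about 13 points (66% to 53%), and the remaining 14 come from the change of level.
- **The estimate is biased.** Matching on pre-treatment variables without regard to outcome mainly costs precision and shifts the population. No bias is demonstrated.

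It is also fair that the power loss needs heavy dropout and a strict caliper together, and that ANCOVA would have more power than the t-test used here if baseline ISI predicts the outcome. These points reduce the size of the problem. They do not supply a reason to match.

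**Conclusion.** Wrong as written. The plan prescribes a procedure with no purpose in a 1:1 randomised trial. The set it would produce cannot be the ITT full analysis population of the same section, and the plan does not rank the two. This is an error in stated text, not a detail left to a later document.

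The numerical consequence is conditional. Only if the matched set is primary are about 4-22% of patients dropped, and only with the full 20% dropout does power fall by about 2 to 11 points, from about 80% to about 69-78%. With little dropout it stays near or above 80%. These figures rest on d = 0.5, the simulated covariate distributions, pair matching, and lost patients contributing no information. The contradiction depends on none of these.

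**What to change.** Delete the matching sentences at the start of 2.11, or keep matching only as an analysis labelled as sensitivity, with the caliper scale, matching order and full variable list fixed in advance.

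State that the primary analysis is an ANCOVA of ISI at week 4 in all patients of the full analysis population, in the arm to which they were randomised, with treatment as factor and baseline ISI as covariate. If balance on age, gender, smoking, drinking or body mass index matters, prespecify those variables and enter them in the same model.

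The cost is a few sentences. No further patients or data are needed, and no randomised patient is lost to matching. Make the change before unblinding, with the ethics committee's agreement where section 2.14 requires it for significant changes.

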**Method:**

This study will be a single-center, double-blind, randomized, parallel group, placebo-controlled clinical trial involving a total of 160 eligible patients aged between 18 and 65. Participants will be randomly assigned to either the intervention group, receiving SHG, or the placebo group receiving placebo granules. Follow-up visits will occur every 2 weeks from baseline to 2 months. The primary outcome is the perceived insomnia severity measured by the Insomnia Severity Index. The secondary outcome measures include the Pittsburgh Sleep Quality Index, Fatigue Severity Scale, Patient Health Questionnaire, Generalized Anxiety Disorder, Visual Fatigue Analogue Scale, Traditional Chinese medicine syndrome score, and Polysomnography.

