**FIGURE 1 F1:**
[figure not shown]
Study flowchart. SHG, Shuhe Granule; ISI, Insomnia Severity Index; PSQI, Pittsburgh Sleep Quality Index; FSS, Fatigue severity scale; PHQ-9, Patient Health Questionnaire; GAD-7, Generalized Anxiety Disorder; PSG, Polysomnography.

**TABLE 2 T2:** A standard protocol items: recommendation for interventions for trials (SPIRIT).

Study phase time	Baseline	Intervention period		Follow up	
	−1∼0 weeks	2 weeks	4 weeks	6 weeks	8 weeks
Data collection at baseline					
Eligibility screen	√				
Informed consent	√				
Demographic data	√				
Allocation	√				
Medical history	√				
Outcome measurements					
ISI	√	√	√	√	√
PSQI	√		√		√
FSS	√		√		√
GAD-7	√		√		√
PHQ-9	√		√		√
PSG	√		√		
Safety evaluation					
Blood routine	√		√		
Urine routine	√		√		
Liver and kidney function	√		√		
Electrocardiogram	√		√		
AEs		√	√	√	√

ISI, Insomnia Severity Index; PSQI, Pittsburgh Sleep Quality Index; FSS, Fatigue severity scale; PHQ-9, Patient Health Questionnaire; GAD-7, Generalized Anxiety Disorder; PSG, Polysomnography; AEs, adverse events.

“√” Represents the need for implementation at this point in time.

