#### 2.8.1 Primary outcome

The primary outcome is the change of ISI score after 4 weeks of intervetion.

ISI consists of seven items, with scores ranging from 0 to 4 for each item, and total scores ranging from 0 to 7 indicating normal sleep, from 8 to 14 indicating mild insomnia, from 15 to 21 indicating moderate insomnia, and from 22 to 28 indicating severe insomnia (Cerri et al., 2023).

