In many clinical assessments, ISI is used to measure the severity of insomnia, and PSQI is often used as an index to measure the overall sleep quality (Niu et al., 2023). In this study, the primary outcome is ISI score at week 4. The ISI is a crucial outcome measure in clinical trials assessing the severity of insomnia in patients. The ISI is a validated self-report questionnaire that provides a comprehensive assessment of the impact of insomnia on an individual’s daily functioning, including sleep satisfaction, sleep interference, and daytime impairment (Bastien et al., 2001). ISI focuses on the subjective symptoms of insomnia, the consequences and the degree of distress, and is sensitive to detect changes in sleep conditions brought about by treatment. However, researchers need to be alert to the possibility of false positive results when patients subjectively amplify their insomnia feelings. Therefore, we also conducted PHQ-9 and GAD-7 to assess the degree of anxiety and depression. Current research has found a strong correlation between insomnia and fatigue (Kim et al., 2019). We believe that SHG can improve both patients’ insomnia and fatigue symptoms, so we also conducted evaluations of FSS. At the same time, we conducted PSG examinations before and after the intervention in order to find objective evidence that SHG improved sleep structure.

The study also has certain limitations. The single-center study may not extrapolate the results to other ethnic groups or regions. Sample size and treatment duration are calculated based on our previous exploratory study, which may lead to an overestimation of the efficacy of SHG. Longer follow-up is needed to observe the impact of SHG on clinical prognosis such as the dosage of western medicine and the recurrence rate of insomnia in patients with chronic insomnia.

In conclusion, this trial will provide high-quality evidence for usage of SHG, hoping to reduce the insomnia severity index and improve clinical symptoms and quality of life of patients with insomnia. Whether the results are neutral, negative, or positive, this trial will have clinical implications for patients with chronic insomnia.

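### The single per-protocol set requires completed follow-up, which runs to week 8, although the primary endpoint is the week-4 ISI change

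*Protocol article*

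**What the plan says.** The protocol article fixes the endpoint at the end of treatment. Section 2.8.1 states: "The primary outcome is the change of ISI score after 4 weeks of intervetion". The Discussion repeats it: "In this study, the primary outcome is ISI score at week 4".

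Observation continues for as long again. Section 2.2 states: "The duration of the intervention is 4 weeks and the total observation follow-up period will be 8 weeks", and "Study visits will take place at baseline and at 2, 4, 6, 8 weeks". Table 2 places weeks 6 and 8 under its follow-up heading, separate from the intervention period at weeks 2 and 4. The abstract also runs follow-up to the end: "Follow-up visits will occur every 2 weeks from baseline to 2 months".

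Section 2.11 names the lead population: "We will conduct preliminary analysis on the full analysis population following the Intention-to-Treat (ITT) principle". I read this as the main analysis. The per-protocol set is a subset of that population and "includes patients who completed the predetermined minimum exposure to trial drug and completed follow-up". The definition has two conditions, both required, with no time limit and no version specific to an endpoint. The article does not say which outcomes or visits will be analysed in this set.

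**The concern.** A per-protocol set for an endpoint should depend on what happened up to that endpoint: whether the patient took enough drug, had the assessment and stayed within the protocol. This definition adds a condition that is settled only later. A patient can take the full 4 weeks of drug, give a week-4 ISI and still lose membership by leaving in week 5.

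Leaving after week 4 need not be unrelated to sleep. The withdrawal rules in section 2.4.5 cover patients who take prohibited or interfering medicines and patients with serious disease-related changes. Neither rule is limited to the treatment period. A patient who sleeps badly off drug could therefore be withdrawn in weeks 5 to 8 and drop out of a comparison of values recorded earlier. If this happens at different rates, or to different kinds of patient, in the two arms, a week-4 per-protocol comparison mixes adherence with retention after the endpoint.

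**Working it through.** **1. Timing.** Primary endpoint: week 4 (sections 2.8.1 and 3). End of follow-up: week 8 (abstract, section 2.2, Table 2). Gap: 8 − 4 = 4 weeks, all off study drug.

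**2. Does the reading of *follow-up* matter?**
- Table 2 sense (weeks 6 and 8): completing it means reaching week 8.
- Section 2.2 sense (the whole 8-week observation): completing it means reaching week 8.
- Looser sense: section 2.7 calls the week-2 visit a follow-up visit, and the full-analysis-set definition in 2.11 uses the word for post-baseline contact in general. The last such visit on the schedule is still week 8.

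No section ends follow-up at week 4.

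**3. Test case.** A patient has full exposure and an observed week-4 ISI, and leaves in week 5.
- Full analysis set: included, with an observed primary outcome.
- Sensitivity analysis without imputation (section 2.11): included for week 4, because the value is observed.
- Per-protocol set as written: excluded.

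**4. The plan's own figure.** Section 2.10 inflates 128 patients for 20% loss: 128 / (1 − 0.20) = 160, or 80 per arm. This reproduces.

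**5. How many could be excluded.** The documents do not split the 20% around week 4, so the split is an assumption, shown as a range. Let L be the share of the 160 lost after week 4, with 20% lost in total by week 8.
- Still in the trial at week 4: N4 = 160 × (1 − (0.20 − L))
- Reaching week 8: 160 × 0.80 = 128, the most the per-protocol set can hold
- Removed by the week-8 condition: N4 − 128

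| L | N4 | Removed | Share of N4 |
|---|---|---|---|
| 0% | 128 | 0 | 0% |
| 5% | 136 | 8 | 5.9% |
| 10% | 144 | 16 | 11.1% |
| 15% | 152 | 24 | 15.8% |
| 20% | 160 | 32 | 20.0% |

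With a constant dropout rate, retention at week 4 is √0.80 = 0.894. Then N4 = 160 × 0.894 = 143.1, and 143.1 − 128 = 15.1 are removed, which is 15.1 / 143.1 = 10.6%. These counts treat everyone present at week 4 as having adequate exposure and an ISI value, so they are upper figures for each split.

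**6. Is precision the issue?** Section 2.10 gives no SD, so assume a standardised difference of 0.5 and one-sided alpha 0.025. With n per arm, power = Φ(0.5 × √(n/2) − 1.96).
- n = 64 (128 in total): Φ(2.83 − 1.96) = 0.81
- n = 72 (144 in total): Φ(3.00 − 1.96) = 0.85
- n = 80 (160 in total): Φ(3.16 − 1.96) = 0.89

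The loss of power is modest. The main concern is selection on behaviour after the endpoint.

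**The case against.** The strongest reply is that this set carries little weight. Section 2.11 assigns it no analysis, endpoint or visit, so a week-4 per-protocol comparison is an inference. The robustness check that the article does state is the sensitivity analysis without imputation, and that analysis keeps the patients in question. Requiring completion of the schedule also gives one common population for weeks 4, 6 and 8, which is defensible for a secondary set. All of this stands, and it limits the point to a supporting analysis.

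A second reply is that the article uses *follow-up* loosely and that a fuller document may give the detail. The looseness is real, but no use of the word in the article ends follow-up at week 4. The point also does not rest on missing detail. The article states a rule, and the rule as stated does not fit the endpoint.

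A third reply is that the mechanism is speculative. Section 2.7.2 provides temporary medication within the trial for patients who do not improve, which weakens the motive to leave. Section 2.4.5 plans to collect evaluations from those who discontinue. Section 2.10 applies the 20% to a sample size based on the primary endpoint, so none of it need fall after week 4; any later loss would then be extra and is not stated. This stands too: the protocol shows that selection is possible, not that it will occur.

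A reader might go further and put a size on the bias. Suppose 8 of 72 week-4 completers in one arm leave and are 2 to 4 ISI points worse than the mean of the 72. That arm's mean then shifts by 8 × 2 / 64 = 0.25 to 8 × 4 / 64 = 0.50 points. The documents support none of the three assumptions: the split of the loss, the difference in the leavers, or its restriction to one arm. Comparing the shift with the pilot's 4.42-point reduction does not help, because that figure is a 2-week, single-arm, within-group change and not a between-arm difference at week 4.

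**Conclusion.** The point holds in a limited form. On the natural reading, the per-protocol definition requires patients to reach week 8. If the set is used for the week-4 primary endpoint, it excludes patients with adequate exposure and an observed outcome because of later, off-drug events that may relate to sleep.

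The count is an assumption-based range of 0 to 32 of 160, taking the 20% as total loss by week 8. It is about 15 if dropout is constant over time. The direction of any bias cannot be determined: it depends on which arm loses patients after week 4 and on how those patients were sleeping at week 4.

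A reader might infer that the primary result is compromised, or that the rule favours SHG. The documents support neither inference. The lead analysis does not use this set, and nothing in the article indicates which arm would lose more patients after week 4. Priority is low to moderate.

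**What to change.** In section 2.11, tie the per-protocol set to the endpoint being analysed. For the primary endpoint, include members of the full analysis set who reached the preset exposure minimum, have a week-4 ISI and had no major deviation before that visit. Require attendance at week 6 or week 8 only for per-protocol analyses of those visits.

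This takes one or two sentences and needs no new data, visits or patients. Section 2.13 sends changes to the research plan to the Ethics Committee before they are implemented, so the edit would follow that route. The small statistical cost is that the per-protocol population differs between visits, so the number analysed should be reported at each one.

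### Missing ISI scores are filled with one value from a regression on an undefined index, then LOCF; depending on what the index means, the week-4 effect can be attenuated or overstated.

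*Protocol article*

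**What the plan says.** The missing-data rule is in section 2.11 (Statistical analysis) of the protocol article. The main method is named: "The linear trend at point method will be employed to substitute missing values". It is then described: "the existing data series will be regressed against an index variable that is scaled from 1 to n". The fitted value from that regression stands in for the missing score. The fallback follows: "In instances where predicted values cannot be determined, the last observation carried forward (LOCF) method will be implemented". One safeguard is planned: "a sensitivity analysis will be performed without imputation to evaluate the robustness of the findings".

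The completed data go into an analysis of covariance with 95% confidence intervals (section 2.11). The primary outcome is the change in ISI after 4 weeks (section 2.8.1), so the rule covers the primary endpoint. ISI is collected at baseline and at weeks 2, 4, 6 and 8 (Table 2), with treatment ending at week 4 (section 2.2). Section 2.10 allows for 20% loss to follow-up, and section 2.11 expects less than 20% of data points to be missing.

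**The concern.** Linear trend at point is a device for filling gaps in a single ordered series. A trial data set has two possible series, and the text does not say which one is meant.

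- **Index over patients (rows 1 to n of the file).** A missing week-4 ISI is predicted from the patient's row number. Arm, baseline ISI and week-2 ISI play no part, and the value changes when the file is re-sorted.
- **Index over one patient's visits.** A patient lost after week 2 has the early change projected in a straight line, so a 4-point fall at week 2 becomes an 8-point fall at week 4. Where only week 4 is missing, the off-treatment visits at weeks 6 and 8 help to set the on-treatment value.

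In both cases one predicted value is entered and analysed as if observed; no residual draw, multiple imputation or variance correction is described. At stake are the primary estimate and its confidence interval.

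**Working it through.** **The plan's own figure.** 128 / (1 − 0.20) = 160, as section 2.10 states. The allowance is therefore 0.20 × 160 = 32 patients.

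**Inputs.** From the protocol: 80 per arm, 1:1 allocation, up to 20% missing, ANCOVA on ISI at week 4. Assumed, because the protocol gives no SD or between-group difference: SD 5, within-patient correlation 0.5, baseline mean 16, placebo change −3, true effect 2.5 points in favour of SHG. Each scenario was simulated 4,000 times. Effects are shown below as points in favour of SHG.

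**Expected estimate by hand.** With a share m missing in each arm, estimate = (1 − m) × true effect + m × effect carried by the filled values.

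- Row index, arbitrary order: both arms receive roughly the same pooled value, so the filled values carry no effect. 0.8 × 2.5 + 0.2 × 0 = 2.0. At 10% missing: 0.9 × 2.5 = 2.25.
- Visit index, linear course (half the effect present at week 2): the filled effect is 2 × 1.25 = 2.5, so the estimate is 2.5.
- Visit index, early plateau (80% of the effect present at week 2): the filled effect is 2 × 2.0 = 4.0. 0.8 × 2.5 + 0.2 × 4.0 = 2.8.
- LOCF alone, linear course: 0.8 × 2.5 + 0.2 × 1.25 = 2.25.

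**Simulation, 20% missing completely at random, true effect 2.5.**

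| Handling | Mean estimate | Mean SE | Empirical SD | Coverage |
|---|---|---|---|---|
| Complete data | 2.52 | 0.685 | 0.688 | 0.945 |
| Observed cases | 2.52 | 0.768 | 0.777 | 0.939 |
| Row index, arbitrary order | 2.01 | 0.639 | 0.645 | 0.883 |
| Row index, sorted by arm | 2.38 | 0.634 | 0.769 | 0.890 |
| Visit index, linear course | 2.52 | 0.880 | 0.872 | 0.951 |
| Visit index, early plateau | 2.80 | 0.893 | 0.898 | 0.938 |
| LOCF alone, linear course | 2.27 | 0.700 | 0.700 | 0.940 |

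**Why coverage falls.** In arbitrary row order the mean SE (0.639) matches the empirical SD (0.645), so the shortfall comes from bias. The half-width is about 1.975 × 0.639 = 1.262 and the bias is 2.5 − 2.01 = 0.49. Coverage ≈ Φ((1.262 − 0.49)/0.645) − Φ((−1.262 − 0.49)/0.645) = Φ(1.20) − Φ(−2.72) ≈ 0.88. In an arm-sorted file the fault is mainly false precision: the mean SE of 0.634 is about 18% below the empirical SD (1 − 0.634/0.769).

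**Other missingness.** If dropout depends on the week-2 response, the row index gives 1.95 with coverage 0.857, and observed cases give 2.48 with coverage 0.948. Across the simulations run, which varied SD and correlation, row-index coverage at about 20% missing was roughly 84–88%. At 10% missing it was about 93%.

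**No true effect.** In arbitrary row order the row index rejects in 5.0% of trials. In a file sorted by arm with about 20% missing, type I error is about 10–11%, falling to about 7% at 10% missing and 6% at 5%. For the visit index with an early plateau and 30% missing on placebo against 10% on SHG, each filled value is 2 × (−2.4) − (−3) = −1.8 points off. The spurious difference is 1.8 × (0.30 − 0.10) = 0.36 points; the simulation gave 0.35 (against SHG) with 7.0% rejection.

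**The case against.** The strongest defence is that the milder reading may be the intended one. LOCF applies only where no prediction can be made. With an index over 160 rows a prediction is essentially always available, so the fallback would have almost no role. It makes sense if the series is a patient's own visits, where a single observation cannot define a line. Against that, the usual SPSS procedure, the software named in section 2.11, runs over cases. The ambiguity stands, and a primary analysis should not depend on resolving it later.

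Three stronger readings are tempting and are not supported.

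- *The rule always biases the effect and always gives wrong intervals.* It does not: the visit index with a linear course gave 2.52 with coverage 0.95. Its cost there is precision (SE 0.880 against 0.768).
- *Type I error doubles.* That needs the row index, a file sorted by arm and about 20% missing together. The protocol states no such sort, and section 2.6 says the statistician is blinded. In arbitrary order the bias is toward no effect.
- *32 of 160 primary values will be imputed.* That is a ceiling. The full analysis set excludes patients who "did not receive any assigned treatment or follow-up", so patients without follow-up would be left out, not filled in. Section 2.4.5 plans to collect evaluation items from those who discontinue, and section 2.12 adds reminder calls.

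The planned analysis without imputation is a real safeguard: observed-case ANCOVA was close to unbiased with near-nominal coverage in these simulations. It can reveal a damaging fill, but it does not correct the headline estimate, and the article does not say what follows if the two disagree.

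The objection that weeks 6 and 8 inform week 4 also applies in part to a joint model of all visits. Such a model, however, estimates a separate mean for each visit and arm and does not force one straight line.

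**Conclusion.** The point holds in conditional form. Section 2.11 fixes a single deterministic fill for the primary endpoint without defining its index. Over patients, at about 20% missing and an assumed effect of 2.5 points, the estimate shrinks by about 20% and coverage falls to about 84–88%. Over visits, it is nearly unbiased with nominal coverage for a linear course but less precise than observed cases, and gives about 2.8–2.9 with an early plateau. In the row-index and plateau settings it does worse than no imputation.

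The direction therefore depends on the reading and on the shape of the course. The size depends on the missing share and on the assumed SD, correlation and effect, none of which the protocol supplies. With 5% missing the row-index coverage in arbitrary order is close to nominal. The rule should still be changed before unblinding, because it governs the primary estimate and better use of the same data is available.

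**What to change.** In section 2.11, delete linear trend at point and LOCF as the primary handling of missing data. Replace them with one of the following:

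- a mixed model for repeated measures on ISI at weeks 2, 4, 6 and 8, with arm, visit, arm-by-visit and baseline ISI, taking the week-4 contrast as primary; or
- multiple imputation by arm from baseline and all ISI visits, followed by the planned ANCOVA at week 4.

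State the missing-data assumption, and keep the observed-case analysis as a sensitivity analysis. A sensitivity analysis that shifts imputed values unfavourably for SHG dropouts, and the place of randomised patients without follow-up in the analysis set, are separate and optional here.

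The cost is a change of wording and a standard procedure. ISI is already collected at every visit, so no patients, visits or measurements are added.
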